**Clinical Study Protocol**

A multicenter, randomized, double-blind, placebo-controlled trial of high-dose rebamipide treatment for low-dose aspirin-induced moderate-to-severe small intestinal damage (CREAM study)

1. Introduction

Aspirin has been used for defervescence and analgesia for a long time; however, in recent years, low-dose preparations with an expected antiplatelet effect have frequently been used. This effect is based on the inhibition of prostaglandin or thromboxane A2 production by the inhibition of cyclooxygenase activity.1 In 2002, the American Heart Association recommended the prophylactic administration of low-dose aspirin (LDA) for the recurrence of ischemic heart disease. This recommendation was based on the finding that LDA inhibited the recurrence of heart disease by 10% during a 10-year observation period.2 Owing to the effect of the recommendation, prophylactic administration of LDA at a dose of 100 mg/day or lower for ischemic heart disease became widely used.

However, despite such clinical contribution, gastrointestinal adverse reactions arose as problems.3-5 A recent case-control study in Japan reported that the administration of LDA increases the risk of upper gastrointestinal bleeding by 5.5-fold compared to that with nontreatment with aspirin.6 To solve this problem, prophylactic administration of antisecretory drugs is recommended worldwide, and clinical trials to obtain the indication are under way in Japan.

Meanwhile, another problem that arose is the presence of cases in which gastrointestinal bleeding other than gastric, duodenal, and large intestinal bleeding is suspected, and the number of patients in 1999 was reported to be as many as 45,000 based on the estimation of the incidence of peptic ulcer (bleeding) of unknown site performed by Japanese the Ministry of Health, Labour and Welfare once every 3 years. Endoscopy through the oral and transanal routes has generally been performed; however, diagnosis in the small intestine, a long organ with a length of approximately 7 m, has been inadequate. Recently, the development of capsule endoscopy and balloon endoscopy has allowed the observation of the entire small intestine, enabling the detection of small intestinal diseases such as small intestinal bleeding and small intestinal tumors.7-9 In Spain, an epidemiologic study in >30,000 subjects has been conducted, and death due to lower gastrointestinal disease was reported in 8.8% in 2005, which was a significant increase compared with the 5.5% rate in 2001. A recent increase in patients taking LDA has been pointed out as one of the causes.10 This is considered to be because of the difficulty of antisecretory drugs to act on the small intestine.

In our previous study, a significant improvement effect was observed after an 8-week administration of misoprostol (prostaglandin preparation) for small intestinal damage (redness and mucosal break) in patients receiving long-term aspirin therapy.11 This finding suggests the possibility that prostaglandin preparations may act on the small intestine. However, because misoprostol is associated with a high incidence of adverse reactions, such as diarrhea, candidate drugs in addition to misoprostol need to be further investigated.

Therefore, we decided to perform an exploratory study by using the antiulcer drug rebamipide as a candidate drug. Rebamipide exerts a wound-healing effect independently of gastric acid, and is expected to be useful against small intestinal damage. Rebamipide has pharmacological effects such as endogenous prostaglandin-increasing, free radical–scavenging, microcirculation-improving, and anti-inflammatory effects, besides its prophylactic effect against nonsteroidal anti-inflammatory drug (NSAID)-induced small intestinal damage that has been reported in animal experiments.12-13 The dose of rebamipide currently approved for gastric ulcer and gastritis is 300 mg/day; however, a dose of 300 mg/day or higher is presumed to be necessary for the small intestine because of its large area. According to a clinical trial report on rebamipide, doses up to 900 mg/day have been investigated in a phase II dose-finding study, and no safety problems were noted.14-15 Therefore, in this exploratory study, we decided to investigate the efficacy of a dose of 900 mg.

**2. Study Objective**

To investigate the healing-promoting effect of rebamipide, a protective drug for LDA-induced small intestinal mucosal damage.

Because there is no evidence for the therapeutic effect of rebamipide against LDA-induced small intestinal damage, this study was created as a pilot study exploring this possibility.

**3. Study Method**

**3.1 Study Subjects**

Patients taking low-dose (enteric) aspirin (brand name, Bayaspirin) for 3 months or longer.

**3.1.1 Inclusion Criteria**

Subjects who meet the following conditions will be registered into this study:

1. Subjects who provided written consent for participation.
2. Subjects who have been receiving treatment with Bayaspirin (100 mg/day or lower) for at least 3 months, and who are scheduled to continue Bayaspirin for the study period of 8 weeks or longer.
3. Patients with diseases such as ischemic heart disease and ischemic cerebrovascular disease whose conditions are stable.
4. Subjects aged 20 years or older.
5. Subjects of both sexes.
6. Subjects with small intestinal damage detected with capsule endoscopy.

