**3.1.3 Handling of Patients**

1) The investigator will provide an adequate explanation about participation in this study, and will obtain consent from participants.

2) If some mucosal damage is observed on small intestinal endoscopy, the investigator will confirm that the subject satisfies the inclusion criteria and does not meet the exclusion criteria, and will register the subject into the study.

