**3.3.5 Method and Period of Administration**

1) Patients with small intestinal damage among those taking Bayaspirin will be randomized into two groups (groups A and B). Capsule endoscopy will be used in the diagnosis of the small intestine. A separately specified controller will perform the allocation.

2) Randomization

Subjects will take the randomly assigned test drug during the study.

Dynamic allocation by using the minimization method will be applied in randomization, and subjects will be allocated to each of the two groups in the study. Drug numbers and information on the allocated groups will be managed by the allocation controller, and will be disclosed when the data are fixed after the completion of the study.

3) Allocated groups and drug administration method:

Group A: Three tablets per dose of control (placebo) tablet (100 mg lactose) will be taken three times daily after every meal.

Group B: Three tablets per dose of rebamipide tablet (100 mg rebamipide) will be taken three times daily after every meal.

4) Administration period: 8 weeks

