**3.4 Evaluation Criteria**

**3.4.1 Primary Endpoint**

Decreasing the number of small intestinal mucosal breaks

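### The entry rule requires neither a mucosal break nor any severity level, although the endpoints and sample size rest on breaks and the title says moderate-to-severe

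*Protocol*

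**What the plan says.** The protocol's title describes the population as having "low-dose aspirin-induced moderate-to-severe small intestinal damage". The rules that decide who enters are wider:

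- Section 3.1.1, criterion 6: "Subjects with small intestinal damage detected with capsule endoscopy".
- Section 3.1.3, item 2, starts registration with the words "If some mucosal damage is observed on small intestinal endoscopy".
- Section 3.3.5, item 1, randomises aspirin users who have small intestinal damage and adds no condition on lesion type, count or grade.

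No exclusion in section 3.1.2 removes patients without a break or with mild damage. The registration center confirms eligibility (section 3.1.4), but the protocol gives it no lesion criterion beyond criterion 6. The Lewis score appears only as a secondary endpoint (section 3.4.2).

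The endpoints are narrower. The primary endpoint (section 3.4.1) is "Decreasing the number of small intestinal mucosal breaks". The first secondary endpoint is complete healing of those breaks. Section 3.7.1.4 sizes the trial on complete healing rates of 20% and 58%, the latter taken from mucosal breaks in an earlier misoprostol study.

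The term damage is not defined. Its only gloss is in the Introduction, where the misoprostol study is said to have shown improvement "for small intestinal damage (redness and mucosal break) in patients receiving long-term aspirin therapy".

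**The concern.** Two mismatches follow.

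First, nothing in the entry rules enforces the severity in the title. This holds even if damage is read as meaning breaks, because a patient with a single break still qualifies. A conclusion about moderate-to-severe damage would then describe a population that the trial did not select.

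Second, a patient with damage but no break satisfies the rules as written. That patient's break count starts at zero and can only stay there or rise. There is nothing to heal, and the protocol gives no healing status for such a case. The assumed 20% and 58% describe the healing of breaks, so they do not apply to this patient. With 15 patients planned on placebo, a few such entrants would matter.

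**Working it through.** **Plan's own figure.** Section 3.7.1.4 gives 30 in the rebamipide group for 90% power at 5%, with 20% v 58% and 10% loss. The pooled two-proportion formula returns 30 with equal arms and a one-sided 5% test: 27 per arm, and 27/0.9 = 30. With the 15:30 split shown in section 3.3.6, two-sided power is 70% before loss. That gap from 90% is a separate matter. It is noted only because it sets the starting point below.

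**Inputs for the illustration.**
- p1 = 0.20 and p2 = 0.58 (section 3.7.1.4).
- Planned arms of 15 and 30 (section 3.3.6) and 10% loss (section 3.7.1.4): 15 × 0.9 = 13.5, taken as n1 = 14; 30 × 0.9 = n2 = 27.
- Two-sided 5%: the protocol does not state sidedness, so this is an assumption.
- Break-free share f = 5% to 30%, equal in both arms on average: an assumption, since the documents give no figure.

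**Formula.** Power = Φ[(|p2 − p1| − 1.96·SE0)/SE1], where
- p̄ = (n1·p1 + n2·p2)/(n1 + n2)
- SE0 = √[p̄(1 − p̄)(1/n1 + 1/n2)]
- SE1 = √[p1(1 − p1)/n1 + p2(1 − p2)/n2]

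**No break-free patients (f = 0).** p̄ = (14 × 0.20 + 27 × 0.58)/41 = 0.450; SE0 = 0.1639; SE1 = 0.1430. Power = Φ[(0.38 − 1.96 × 0.1639)/0.1430] = Φ(0.41) = 66%.

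**Three ways of handling break-free patients.**
- Counted as not healed: each rate becomes (1 − f)p.
- Counted as healed: each rate becomes (1 − f)p + f.
- Left out: rates unchanged, arm sizes multiplied by (1 − f).

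In the first two the difference shrinks to 38(1 − f) points. For example, at f = 20% and counted as not healed, the rates are 0.160 v 0.464, p̄ = 0.360, SE0 = 0.1581 and SE1 = 0.1372. Power = Φ[(0.304 − 0.3099)/0.1372] = Φ(−0.04) = 48%.

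| Assumed f | Difference if counted (points) | Not healed | Healed | Left out |
|---|---|---|---|---|
| 0% | 38.0 | 66% | 66% | 66% |
| 5% | 36.1 | 62% | 60% | 63% |
| 10% | 34.2 | 57% | 55% | 61% |
| 20% | 30.4 | 48% | 46% | 55% |
| 30% | 26.6 | 40% | 38% | 49% |

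**Primary endpoint.** No power is computed, because the protocol gives no expected reduction or spread for the break count. The direction can be reasoned. Section 3.7.1.2 names paired tests of baseline against 8 weeks. The standard Wilcoxon signed-rank test drops a patient who has zero breaks at both visits, and McNemar's test gets nothing from a patient whose status does not change. Under those tests the loss is in effective sample size. In a comparison of mean change between arms, the same patients would attenuate the difference.

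**The case against.** The best counter-argument is that the Introduction's mention of redness reports findings of an earlier study and does not define criterion 6. Elsewhere the protocol leans towards breaks: it speaks of wound healing, and its endpoints and sizing are break-based. Investigators may well have enrolled only patients with breaks. This stands. A reader might infer that the protocol deliberately admits redness-only patients, but the text supports only that the term is undefined and nothing narrows it.

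A reader might also infer that the treatment comparison would be biased. It would not. Having no break is known before randomisation. Counting such patients the same way in both arms attenuates the difference, and leaving them out by a rule based on the baseline reading only reduces numbers. Neither favours an arm.

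Third, sections 2 and 3.2 present an exploratory pilot, in which broad entry is defensible. That softens the severity part, which dropping a word from the title would cure. It does not explain admitting patients who cannot contribute to the primary endpoint, and the trial still tests at 0.05 and claims a powered sample size.

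Investigator discretion (exclusion 9) could screen out such patients, but it is not a lesion criterion and may vary between sites. An analysis plan could leave them out by a baseline rule, at the cost in the last column of the table. It could not replace them.

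**Conclusion.** The point holds as a mismatch between the entry rules and both the title and the break-based endpoints; it should be corrected. The title mismatch rests on the text alone. The break-free problem rests on an undefined term and on a share of patients that the documents do not give and that could be near zero.

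If that share were 5% to 30%, power for complete healing would fall from 66% to between 62% and 40%, 60% and 38%, or 63% and 49%, depending on handling. These figures illustrate a between-arm test of the secondary healing endpoint. They should not be read as the loss on the primary break count, which cannot be computed from the protocol. Nor is the distance from the stated 90% down to 66% caused by the eligibility wording; it comes from the planned split, the expected loss and the two-sided test assumed here.

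**What to change.** In section 3.1.1 criterion 6, section 3.1.3 item 2 and section 3.3.5 item 1, require at least one small intestinal mucosal break on the baseline capsule. Record the baseline break count on the registration form so that the center can check it before allocation. The center works from faxed forms, so it can confirm the recorded count but not the images.

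Reconcile the title with the entry rule, either by dropping the severity term or by stating the threshold that the sponsor intends by it. Which of these, and what threshold, is the sponsor's choice.

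The cost is one line in three sections and one field on a form. No new procedure is needed, since the baseline capsule is already scheduled. Break-free patients become ineligible, so screening takes somewhat longer. A severity threshold, if the sponsor chooses one, would narrow the pool further, which matters with case accumulation ending on August 31, 2014 (section 7).

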**3.1.2 Exclusion Criteria**

The following subjects will be excluded from the study:

1. Subjects with small intestinal lesions other than LDA-induced small intestinal damage, such as Crohn’s disease and small intestinal tumor.
2. Subjects taking drugs that may induce small intestinal damage such as NSAIDs and anticancer drugs.
3. Subjects taking drugs that may improve small intestinal lesions such as antibiotics, sulfasalazine, prostaglandin preparations, steroids, free radical inhibitors, elastase inhibitors, and gastric mucosa–protecting agents.
4. Subjects with overt bleeding from the small intestine.
5. Subjects with small intestinal diverticula and membranous stenosis.
6. Subjects with significantly decreased renal and hepatic function.
7. Subjects with a history of hypersensitivity to rebamipide.
8. Subjects who participated in other studies within 4 weeks before participation in this study.
9. Subjects judged to be inappropriate by the subinvestigator and the principal investigator.

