**3.3.4 Concomitant Drugs**

1) As described in the exclusion criteria in 3.1.3, drugs that affect the degree of small intestinal mucosal damage will be prohibited in principle during the study.

2) Drugs other than the above-mentioned prohibited concomitant drugs that have been used since before the initiation of administration of rebamipide can be concomitantly used as long as the dose is maintained constant during the study.

3) If patients with active gastric ulcer and duodenal ulcer are treated, an antisecretory drug (proton pump inhibitor, omeprazole) should be administered as necessary. However, mucosal protectants such as rebamipide should not be administered.

4) In patients taking mucosal protectants, the drugs should be discontinued by 2 weeks before capsule endoscopy.

5) If drugs other than the study drug are used, the drug name, dose, and administration period should be entered in the investigation form.

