**3.3.6 Contents and Schedule of Examination**

**Study design**

**Group A**

**(n=15)**

**Group B**

**(n=30)**

**Ｃａｐｓｕｌｅ　ｅｎｄｏｓｃｏｐｙ**

**pre**

**Ｂｌｏｏｄ　ｔｅｓｔ**

**Objective symptom**

**4 weeks**

**8 weeks**

**Ｓｕｂｊｅｃｔｉｖｅ　ｓｙｍｐｔｏｍ**

**3.3.6 Observation Items**

Subject background: Specified at registration

ID assigned by randomization, date of birth, sex, height, body weight, body mass index, drinking history (years), smoking history (years), underlying disease, complications, and used drugs (drug name, dose, and period of use)

Treatment compliance: Status of the administration of the drug

Hematology: Before administration, after administration (4 weeks), and at the completion of treatment (8 weeks)

Red blood cells (104/μL), white blood cells (104/μL), hemoglobin (g/dL), albumin (g/dL), hematocrit (%), total protein (g/dL), glutamic oxaloacetic transaminase (IU/L), glutamic pyruvic transaminase (IU/L), blood urea nitrogen (mg/dL), creatinine (g/day), iron (μg/dL), and C-reactive protein (μg/dL)

Subjective and objective symptoms: Before administration, after administration (4 weeks), and at the completion of treatment (8 weeks)

Subjective symptoms: Epigastric pain, abdominal distension, anorexia, heartburn, stomach heaviness, nausea, vomiting, belching, etc.

Objective symptoms: Epigastric tenderness, hematemesis, melena, etc.

Small intestinal endoscopy: Before administration and at the completion of treatment (8 weeks)

Stool frequency, abdominal symptoms, etc. (after examination; abdominal symptoms and capsule excretion symptoms will be confirmed)

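### Exclusions 2 and 3 cover only current use of lesion-causing and lesion-improving drugs; apart from mucosal protectants, none has a drug-free interval before the baseline capsule

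*Protocol*

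**What the plan says.** The relevant text is in four places in the Protocol.

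- **3.1.2, exclusions 2 and 3.** The lesion-causing drugs are handled by excluding "Subjects taking drugs that may induce small intestinal damage such as NSAIDs and anticancer drugs". The lesion-improving drugs are handled by excluding "Subjects taking drugs that may improve small intestinal lesions such as antibiotics, sulfasalazine, prostaglandin preparations, steroids" and several further classes, gastric mucosa-protecting agents among them. Neither item mentions past use. Exclusion 8 in the same list does carry a look-back: "Subjects who participated in other studies within 4 weeks before participation in this study".
- **3.3.4 Concomitant Drugs.** Item 1 says that "drugs that affect the degree of small intestinal mucosal damage will be prohibited in principle during the study", which begins with the study. Item 4 is the only rule that reaches back before the capsule: "In patients taking mucosal protectants, the drugs should be discontinued by 2 weeks before capsule endoscopy".
- **3.1.2, exclusions 1 and 9.** Exclusion 1 is worded by cause. It begins "Subjects with small intestinal lesions other than LDA-induced small intestinal damage, such as Crohn" and gives Crohn's disease and small intestinal tumor as its examples. Exclusion 9 leaves unsuitable subjects to the investigators' judgment.
- **3.3.6 Observation Items.** The background data specified at registration include "used drugs (drug name, dose, and period of use" and so already cover drug history.

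The objective in section 2 is specific about cause: "To investigate the healing-promoting effect of rebamipide, a protective drug for LDA-induced small intestinal mucosal damage".

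**The concern.** The trial sets out to measure healing of aspirin-induced damage while aspirin continues (3.1.1, inclusion 2). That requires a baseline capsule showing aspirin damage and little else.

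The protocol recognizes that recent drug use can distort the baseline, since it makes mucosal protectants stop 2 weeks beforehand. It gives no such interval to NSAIDs and anticancer drugs, the drugs it names as causing damage. Nor does it give one to antibiotics, sulfasalazine, steroids or the other lesion-improving drugs. Prostaglandin preparations are covered only if a site counts them as mucosal protectants, which the text does not settle.

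Two distortions are possible, in opposite directions:

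- **Recently stopped NSAID.** Some baseline breaks may be due to the NSAID. The drug then stays prohibited, and adding it is a dropout criterion (3.5, item 3), so those breaks may improve whatever the assignment.
- **Recently stopped lesion-improving drug.** The baseline break count may be held down by the earlier drug, and the change to week 8 then starts from too low a value.

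In both cases the change from baseline is partly a response to stopping another drug.

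**Working it through.** **Step 1: what the rules do with a recent stopper.** Take a subject who ended an NSAID course the day before the baseline capsule.

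| Rule | Effect on this subject |
|---|---|
| Exclusion 2 (3.1.2) | Not met: the subject is no longer taking the drug |
| 3.3.4 item 1 | Not breached: it applies during the study |
| 3.3.4 item 4 | Does not apply: an NSAID is not a mucosal protectant |
| Exclusion 1 | Could apply, but no rule is given for telling an NSAID break from an aspirin break |
| Exclusion 9 | Could apply, at discretion |
| Central registration (3.1.4) | Checks eligibility; no criterion refers to past use of these drugs |

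No listed drug criterion removes the subject. The same holds for a recently stopped steroid or antibiotic under exclusion 3.

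**Step 2: the plan's own figures.** Section 3.7.1.4 assumes complete healing of 20% on placebo and 58% on rebamipide, a difference of 38 points, with 10% dropout, 90% power and a 5% level. For 1:1 allocation with pooled variance:

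n = [z_α √(2 p̄(1 − p̄)) + z_β √(p₁q₁ + p₂q₂)]² / Δ², with p̄ = 0.39 and Δ = 0.38.

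One-sided: n = [1.645 × 0.690 + 1.282 × 0.635]² / 0.1444 = 26.3, so 27 per arm, and 27 / 0.9 = 30. This matches the stated 30. Two-sided, the result is 33 per arm, or 37 after dropout. The protocol does not state the number of sides, and the design figure in 3.3.6 shows 15 and 30 subjects.

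**Step 3: dilution.** Suppose a fraction f of each arm are recent NSAID users who heal at rate h in both arms. Both f and h are assumptions; the protocol gives neither.

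- Placebo: (1 − f) × 20% + f × h
- Rebamipide: (1 − f) × 58% + f × h
- Difference: 38 × (1 − f) points

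| f | Placebo healing, h = 50% to 80% | Difference (points) |
|---|---|---|
| 0 | 20% | 38.0 |
| 10% | 23% to 26% | 34.2 |
| 20% | 26% to 32% | 30.4 |
| 30% | 29% to 38% | 26.6 |

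The formula assumes no rebamipide effect in these subjects. If rebamipide raised their healing by d points, the difference would be 38 × (1 − f) + d × f. With d = 19 and f = 10% that is 34.2 + 1.9 = 36.1 points.

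**Step 4: power, as an illustration.** Power = Φ{[Δ − 1.96 √(p̄(1 − p̄)(1/n₁ + 1/n₂))] / √(p₁q₁/n₁ + p₂q₂/n₂)}, two-sided 5%, with h = 80%.

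- 15 and 30 subjects, f = 0: p̄ = 0.453; (0.38 − 0.309) / 0.137 = 0.52, so 70%.
- 15 and 30 subjects, f = 10%: rates 26.0% and 60.2%, p̄ = 0.488; (0.342 − 0.310) / 0.144 = 0.22, so 59%.
- 27 evaluable per arm: 84% at f = 0 and 73% at f = 10%.

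Varying h from 60% to 90% moves the f = 10% results by about one point.

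**Step 5: small arm.** With 15 placebo subjects, one healed subject is 1/15 = 6.7 points of that arm's healing rate.

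**Step 6: the specified tests.** Section 3.7.1.2 names the Wilcoxon signed-rank and McNemar tests between baseline and 8 weeks. They are within-group tests, so improvement after NSAID withdrawal counts as improvement in whichever arm it occurs. Concurrent placebo does not remove it from such a test.

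**The case against.** The other side has several sound points.

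- **Registration needs more than visible damage.** Under 3.1.3 the investigator must also confirm every inclusion and exclusion criterion, and under 3.1.4 the registration center checks eligibility again. This stands, but both checks are made against criteria that do not mention past use.
- **Exclusions 1 and 9 can catch the case.** Crohn's disease and tumor are only examples in exclusion 1, and an investigator may attribute lesions from the recorded drug history. This stands in part. It makes enrollment possible rather than certain, but sites may differ because no rule says how to use the history.
- **The size is assumed.** Nothing in the protocol gives f or h, and an f of 20% to 30% has no support there. The Introduction cites animal work suggesting that rebamipide protects against NSAID damage, so zero effect in these subjects is the pessimistic end. The arithmetic also concerns complete healing, a secondary endpoint, while the primary endpoint is the decrease in number of breaks. All of this stands.
- **The study is a randomized, blinded pilot.** A between-group comparison would be diluted, not biased toward rebamipide. This stands for that comparison, but not for the within-group tests.

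A reader might infer that none of the lesion-improving drugs has an interval. That is wrong, because mucosal protectants have 2 weeks. A reader might also infer that the same 2 weeks would be enough after an NSAID. The protocol gives no basis for that; it says nothing about how long NSAID lesions last.

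**Conclusion.** The gap is real and narrow. For NSAIDs, anticancer drugs, antibiotics, sulfasalazine, steroids and the other drugs in exclusions 2 and 3 apart from mucosal protectants, the rules followed exactly do not exclude a subject who stopped just before the qualifying capsule. That subject's baseline may not be aspirin damage, or may be suppressed. Analysis cannot fully repair this afterwards, because it is settled at enrollment.

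The effect cannot be sized from the protocol. At an assumed f of 10%, with equal healing in both arms, the planned difference falls from 38 to about 34 points. Two-sided power at 15 and 30 subjects falls from 70% to 59% if those subjects heal at 80%. The suppressed-baseline case is not quantified.

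A reader might go further and conclude that such subjects will be enrolled, will heal naturally in either arm, and will make rebamipide look better than it is against placebo. The documents do not support this. Exclusions 1 and 9 may remove some of them, no healing rate after withdrawal is given, and the likely effect between groups is dilution. The point is a cheap improvement to eligibility and does not show that the trial's result would be wrong.

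**What to change.** Reword exclusions 2 and 3 so that each covers subjects *taking, or having taken within a stated interval before the baseline capsule endoscopy,* the listed drugs. The sponsor should set the interval for each drug class, give its reason, and reconcile it with the 2 weeks in 3.3.4 item 4. The text should also say whether prostaglandin preparations count as mucosal protectants for that item.

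Have the central registration center check the interval against the period of use recorded at registration. If the registration form, which is not shown, does not already display the date of last use, add that field.

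The cost is a clause in two criteria and one check at registration. The downside is that a few recent users are deferred or not enrolled, which matters somewhat in a trial of this size.
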